# The effect of tapered flow resistive loading inspiratory muscle training on respiratory function in post-stroke tracheostomy patients: study protocol for a parallel-group, assessor-blinded randomized controlled trial

**DOI:** 10.3389/fneur.2025.1625289

**Published:** 2025-09-03

**Keywords:** stroke, tracheostomy, tapered flow resistive loading, maximum inspiratory pressure, inspiratory muscle training, decannulation success rate

## Abstract

**Background:**

Post-stroke tracheostomy patients frequently exhibit diverse levels of respiratory dysfunction. Inspiratory muscle training has demonstrated efficacy as an intervention to enhance respiratory function in these patients. However, conventional methods of inspiratory muscle training often fall short in terms of load regulation and individual adaptability. Tapered Flow Resistive Loading Inspiratory Muscle Training (TFRL-IMT) represents an innovative training modality that offers distinct advantages in augmenting respiratory muscle function. Nonetheless, its application in post-stroke tracheostomy patients remains under-researched, necessitating further systematic investigation to ascertain its clinical value.

**Methods and analysis:**

This investigation will employ a single-center, assessor-blinded, parallel-group randomized controlled trial design, enrolling 60 post-stroke tracheostomy patients (planned age range 18–70 years; and gender distribution will be collected and analyzed). Stratified compartmental group randomization will be utilized to allocate participants to either the experimental (*n* = 30) or control group (*n* = 30) in a 1:1 ratio. Both groups will receive conventional treatment, while the experimental group will additionally undergo TFRL-IMT using an electronic device that provides inspiratory resistance which dynamically decreases with increasing lung volume for a duration of three weeks. The primary outcome measure will be the rate of successful decannulation, with secondary outcomes encompassing diaphragm function, respiratory parameters, clinical outcomes, and quality of life assessments. The primary outcome (decannulation success rate) will be compared between groups using the Chi-square test.

**Discussion:**

TFRL-IMT may enhance respiratory function in patients through several mechanisms, including the provision of dynamic loading that aligns with the pressure-volume relationship of the respiratory muscles, the facilitation of neuromuscular adaptive changes, the optimization of the oxidative capacity of respiratory muscle fibers, and the remodeling of the central control pattern of the respiratory muscles. Nonetheless, the current study is subject to certain limitations, including its single-center design, a relatively short follow-up period, and some degree of device dependence and a high degree of heterogeneity in the stroke patient population.

**Clinical trial registration:**

https://www.chictr.org.cn/, identifier ChiCTR2500097604.

## Introduction

Stroke is one of the leading cause of disability and mortality worldwide. According to the Global Burden of Disease Study (GBD) 2021 data, there are approximately 11.9 million new cases of stroke globally each year, with a total prevalence reaching up to 93.8 million (1). In the clinical management of acute stroke, about 10% of patients require endotracheal intubation and mechanical ventilation support (2). As treatment advances, 15–35% of these patients necessitate a tracheotomy to sustain long-term ventilatory support due to delayed recovery of respiratory function (3). Even after successful weaning from mechanical ventilation, 26.5% of patients still require retention of the tracheal tube (4), and only 59% of stroke patients who undergo tracheotomy are successfully extubated within 12 months (5).

Post-stroke tracheostomy patients present significant challenges in their clinical management (6). These patients frequently manifest varying degrees of respiratory dysfunction, including reduced respiratory muscle strength (7), abnormal breathing patterns (8), impaired airway defense mechanisms (9), and diminished vital capacity (10). Although tracheotomy can effectively maintain airway patency, it also prolongs the patients’ hospital stay, escalates healthcare expenditures, and elevates mortality risk and complication rates, with common complications including pneumonia, airway stenosis, and ventilation-associated lung injury (11). From a pathophysiological perspective, prolonged tracheotomy status induces respiratory muscle dysfunction (8), which subsequently results in attenuated cough reflex and compromised airway clearance, and these factors interact with each other to form a vicious circle that impedes successful decannulation (9, 12). A systematic review demonstrated that successful decannulation in post-stroke tracheostomy patients was closely related to the recovery of respiratory muscle function, suggesting that improving respiratory muscle function may be one of the key factors to facilitate decannulation (13).

Inspiratory Muscle Training (IMT) represents a therapeutic intervention that utilizes resistance to enhance strength and endurance of respiratory musculature. Clinical evidence substantiates that IMT significantly enhances respiratory muscle performance in patient (14). Several studies have indicated that IMT enhances not only respiratory muscle strength but also coughing efficacy and accelerates pulmonary functional recovery (15, 16). Moodie et al. (17) conducted a systematic review validating the therapeutic efficacy of IMT for improving respiratory muscle function in mechanically ventilated patients, particularly among tracheostomized individuals with impaired respiratory muscle strength. Their analysis revealed that IMT significantly augments both maximum inspiratory pressure (MIP) and maximum expiratory pressure (MEP). Furthermore, a randomized controlled trial demonstrated improved MIP, higher success rates of ventilator weaning, and reduced hospitalization duration among mechanically ventilated patients undergoing IMT protocols (18). Studies in patients with neurological disorders indicate that regular IMT not only improves respiratory function, but also improves vital capacity and inspiratory reserve capacity, which is clinically important for the tracheotomy decannulation process (19).

Although IMT has achieved significant results in clinical practice, there are still many limitations of the conventional IMT method. Conventional threshold loading equipment is simple in structure and cannot dynamically adjust the loading intensity according to the different lung volume levels of patients, which leads to suboptimal training outcomes (20); Furthermore, conventional IMT mode lacks real-time feedback mechanisms and progress monitoring capabilities, which makes it difficult to maintain patient adherence and ensure the quality of training (21). Current IMT approaches are not individually designed to meet the different pathophysiological mechanisms, especially for patients with neuromuscular diseases, which do not fully consider their special respiratory dysfunction patterns, thus limiting the further improvement of clinical efficacy (22). Most conventional IMT adopts a fixed resistance design, which is not able to adapt to the dynamic demands of the whole respiratory cycle of the patient. This limitation is particularly pronounced during peak inspiratory phases, culminating in diminished training efficacy (23).

Tapered Flow Resistive Loading Inspiratory Muscle Training (TFRL-IMT) is a novel technique for strengthening inspiratory muscles. It delivers a flow resistance load that progressively decreases as lung volume increases, using an electronically controlled resistance valve system, which is designed to better match the pressure–volume characteristics of the respiratory muscles, thereby addressing the limitations of traditional training methods (24). Compared to conventional threshold-loading training, TFRL-IMT offers more uniform loading throughout the respiratory cycle, resulting in greater lung volume expansion and elevated inspiratory flow rates at equivalent training intensities, thereby increasing the total inspiratory workload (23). Modern TFRL-IMT devices incorporate electronic control systems with data storage capabilities, enabling the recording and monitoring of training parameters (25), a functional feature that helps to improve training quality and provides an objective basis for evaluation. Clinical studies have demonstrated that electronic IMT devices are feasible and safe for critically ill patients requiring prolonged mechanical ventilation, with high levels of patient acceptance (26). These findings constitute preliminary evidence supporting the application of TFRL-IMT in post-stroke tracheostomy populations.

Current research on TFRL-IMT has primarily focused on mechanically ventilated patients or individuals with chronic obstructive pulmonary disease (COPD), whereas studies involving post-stroke tracheostomized patients remain relatively scarce. Most existing studies on this population have concentrated on short-term improvements in physiological parameters, with limited systematic evaluation of long-term clinical outcomes. Therefore, further high-quality clinical trials are warranted to address this research gap and to elucidate the therapeutic potential of TFRL-IMT in post-stroke tracheostomized patients.

Therefore, the primary aim of this randomized controlled trial is to evaluate the effects of TFRL-IMT on respiratory function, respiratory muscle strength, decannulation rate, and health-related quality of life in post-stroke patients with tracheostomies. The study hypothesized that a structured TFRL-IMT program would be more effective than conventional respiratory rehabilitation methods in enhancing respiratory muscle strength, improving pulmonary function parameters, facilitating tracheostomy decannulation, and enhancing patients’ quality of life. This research is anticipated to offer a novel therapeutic approach for the clinical management of post-stroke tracheostomy patients and to establish a standardized and generalizable respiratory muscle training program, which is expected to significantly improve the long-term prognosis and functional recovery in this patient population.

## Methods and analysis

### Study design

This study is a single-centre, evaluator-blinded, parallel-group randomised controlled trial aimed at evaluating the clinical efficacy of TFRL-IMT in post-stroke tracheostomized patients. The trial will be conducted at Guangdong Sanjiu Brain Hospital from March 2025 to February 2027. The detailed study procedures are illustrated in Figure 1.

**Figure 1 fig1:**
[figure not shown]
Trial flowchart. Diaphragmatic function assessment will include diaphragmatic mobility and diaphragmatic thickness. Respiratory function parameters will include MIP, FVC, PEF, and FEV1. Clinical outcome evaluation will include length of hospital stay, incidence of respiratory-related complications, and re-intubation rate within 72 h after decannulation. Quality of life assessment will include the EQ-5D-5L Health-Related Quality of Life Questionnaire, the Breathing Difficulty Assessment (Borg Scale), and the Hospital Anxiety and Depression Scale (HADS).

### Participants and recruitment

This study is set to be conducted conducted within the Department of Rehabilitation Medicine at Guangdong Sanjiu Brain Hospital (Guangzhou, Guangdong, China), and will include a total of 60 post-stroke tracheostomy patients. The process for screening study participants will proceed as follows: first, newly admitted patients will be identified the hospital’s electronic medical record system. Rehabilitation physicians will then perform a preliminary evaluation of individuals who may be eligible. For those patients who preliminarily satisfy the inclusion criteria, researchers will engage in face-to-face discussions with them and their families to thoroughly explain the study’s objectives, methodology, and potential risks. Upon obtaining the patients’ consent to participate, researchers will undertake a comprehensive assessment to ensure that all inclusion criteria are met and that no exclusion criteria apply. Ultimately, eligible patients or their legal representatives will be required to sign a written informed consent form and will be formally enrolled in the study.

Baseline demographic and clinical characteristics, including age, gender distribution, stroke type (ischemic/hemorrhagic), and time since stroke, will be documented during enrollment and reported in subsequent outcome publications.

Inclusion criteria: (1) aged between 18 and 70 years; (2) first-evert or recurrent stroke (ischaemic or haemorrhagic) confirmed by cranial CT or MRI; (3) haemodynamically stable, defined as systolic blood pressure between 90–180 mmHg and diastolic pressure between 60–100 mmHg, without the need for vasoactive medication; (4) patients with stroke-related complications (e.g., impaired consciousness, dysphagia or respiratory failure) who underwent tracheotomy and remained clinically stable for ≥72 h post-procedure; (5) Glasgow Coma Scale score of ≥12, and the ability to comprehend and follow simple commands; (6) the patient or their legal representative is capable of understand the study protocol and provide written informed consent.

Exclusion criteria: (1) neuromuscular disorders (e.g., myasthenia gravis, amyotrophic lateral sclerosis) or primary thoracic deformity; (2) comorbid moderate-to-severe lung disease (e.g., COPD, interstitial lung fibrosis) or active pulmonary infection; (3) myocardial infarction, acute heart failure, or unstable cardiac arrhythmia within the past 3 months; (4) pneumothorax within the past month or presence of high-risk factors for pneumothorax; (5) use of medications that may impair neuromuscular function or induce drowsiness (e.g., high-dose sedatives, muscle relaxants); (6) participation in other interventional studies that may influence respiratory function during the same period; (7) expected survival of less than 3 months; (8) severe cognitive impairment that precludes completion of assessment or training procedures.

### Sample size calculation

The sample size calculation for this study was based on data obtained from a pre-trial conducted between October 2024 and January 2025. In the pre-trial, 24 post-stroke tracheostomy patients meeting the study’s inclusion and exclusion criteria were enrolled and randomly assigned to either the TFRL-IMT group (*n* = 12) or the conventional treatment group (*n* = 12). In the conventional treatment group, 6 patients were successfully extubated, resulting in a 50% decannulation success rate. In the TFRL-IMT group, 10 patients were extubated, with an decannulation success rate of 83.3%. The between-group difference in decannulation success rates was 33.3%. Based on the preliminary results and relevant literature (5), the decannulation success rate was conservatively estimated to be 50% in the control group and 80% in the TFRL-IMT group, yielding an expected effect size of 30%.

The sample size was calculated using PASS 15.0 software (NCSS, LLC, Kaysville, UT, United States). A significance level of *α* = 0.05 (two-sided) and statistical power (1 − *β*) = 80% were adopted based on literature recommendations (27). Assuming an decannulation success rate of 50% in the control group and 80% in the TFRL-IMT group, the required sample size for each group was calculated to be 26. Based on the preclinical follow-up experience of the research team, an expected attrition rate of 15% was applied. According to the adjustment formula *n*’ = *n*/(1 − f), where *n* is the unadjusted sample size and f is the expected attrition rate (28), the adjusted sample size per group was calculated as *n*’ = 26/(1–0.15) ≈ 30. Therefore, the finalised total sample size was determined to be 60.

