#### Primary outcome

The primary outcome will be the decannulation success rate following the 3-week intervention. Successful decannulation will be defined as the absence of reintubation within 72 h following tracheostomy tube removal. The decannulation process will adhere to a strictly standardised protocol, with specific criteria as follows: minimal secretions with effective clearance; good cough function (peak cough flow >160 L/min); absence of hypoxaemia (SpO2 ≥ 92%), respiratory distress, or reduced level of consciousness during a 24 h continuous tracheostomy tube occlusion test; and normal swallowing function. The decannulation success rate will be calculated as the proportion of successful decannulation relative to the total number of cases treated and expressed as a percentage. This outcome will be assessed at the end of the 3-week intervention.

Decannulation failure will be defined as the occurrence of any of the following conditions within 72 h post-decannulation: severe respiratory distress (respiratory rate >35 breaths/min); persistent hypoxaemia (requiring FiO2 > 0.5 to maintain SpO2 ≥ 90%); hypercapnia (PaCO2 > 50 mmHg and pH < 7.30); or clinical need for reintubation.

To ensure objectivity and accuracy, decannulation decisions will be made jointly by at least two therapists and rehabilitation physicians who are blinded to patient group allocation. This double-blind assessment design minimizes bias and enhances the reliability of study outcomes.

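### The 12-month literature rate cannot support the 50% control rate at 3 weeks, and 60 patients do not give the stated 80% power even if 50% versus 80% is right

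*Protocol article*

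**What the plan says.** The Sample size calculation section names two supports for the control rate: "Based on the preliminary results and relevant literature (5), the decannulation success rate was conservatively estimated to be 50% in the control group". The first is a randomised pilot of 24 patients who met the trial's own eligibility criteria: "In the conventional treatment group, 6 patients were successfully extubated, resulting in a 50% decannulation success rate". Its treated arm had 10 of 12 (83.3%). The second is reference 5, which the Introduction describes in these words: "only 59% of stroke patients who undergo tracheotomy are successfully extubated within 12 months (5".

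The planning sentence continues with "80% in the TFRL-IMT group, yielding an expected effect size of 30" percentage points. The design values are a significance level of "0.05 (two-sided) and statistical power" of "80% were adopted based on literature recommendations (27"), from which "the required sample size for each group was calculated to be 26". An allowance of 15% for attrition takes this to 30 per group and 60 in total.

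The Primary outcome section counts a decannulation as successful if there is no reintubation within 72 hours of tube removal. On timing it says: "This outcome will be assessed at the end of the 3-week intervention".

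**The concern.** A cumulative 12-month proportion and a proportion at the end of 3 weeks are different quantities, and the article offers no bridge from one to the other. Citing the first for the second makes the control rate look better supported than it is. Without that citation, the rate rests on 12 pilot controls.

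The power claim is a second matter. If the trial has clearly less than 80% power for the effect it was designed to find, a non-significant result is more likely than the reader is told and says less about the absence of an effect. A control rate described as conservative would add to that misreading.

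**Working it through.** **1. Do the sources match the endpoint?**

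| Item | Success | Time point |
|---|---|---|
| Primary outcome | no reintubation within 72 h of tube removal | end of 3 weeks |
| Reference 5, as reported in the Introduction | extubated | within 12 months |
| Pilot (Sample size calculation) | reported as a decannulation success rate; 72 h rule not mentioned | not stated |

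Reference 5 fails on the time point. The pilot can be used, but whether it matches cannot be confirmed from the text.

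**2. How precise is the pilot?** The Clopper-Pearson 95% interval for 6/12 is 21% to 79%; for 10/12 it is 52% to 98%. The planning control rate is 6/12 = 50%, unchanged. Only the treated rate was lowered, from 83.3% to 80%, so the difference fell from 33.3 to 30 points.

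**3. Does n = 26 follow from the stated inputs?** Inputs, all from Sample size calculation: p1 = 0.50, p2 = 0.80, two-sided 0.05 (z = 1.960), power 80% (z = 0.842), 1:1 allocation.

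- Unpooled: n = (1.960 + 0.842)² × (0.50×0.50 + 0.80×0.20) / 0.30² = 7.849 × 0.41 / 0.09 = 35.8, so 36.
- Pooled, mean rate 0.65: n = [1.960 × √(2×0.65×0.35) + 0.842 × √0.41]² / 0.30² = (1.322 + 0.539)² / 0.09 = 38.5, so 39.
- Arcsine gives 38; with continuity correction, 45.
- One-sided versions give 29 to 37.

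The stated 26 is not reproduced by any of these. In addition, 26/0.85 = 30.6, which rounds up to 31, not 30.

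**4. What power do 60 patients give?** Exact power sums the binomial probabilities of all tables in which the uncorrected chi-square test reaches two-sided 0.05, at 50% versus 80%:

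- 30 per arm, all evaluable: 69%
- 26 per arm (30 × 0.85 = 25.5, about 26): 65%
- 39 per arm: 81%

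The Statistical analysis section also allows Fisher's exact test. Its power is 60% with 30 per arm and 54% with 26.

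**5. What if the control rate is below 50%?** The documents give no other 3-week rate, so the lower rates and the effect models below are assumptions. Exact chi-square power, 30 per arm:

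| Control rate | Constant gain of 30 points | Constant ratio 1.6 (80/50) | Treated rate fixed at 80% |
|---|---|---|---|
| 50% | 69% | 69% | 69% |
| 40% | 66% | 47% | 91% |
| 30% | 66% | 29% | 99% |

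A lower control rate reduces power strongly under one model, hardly at all under the second, and raises it under the third.

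**The case against.** The strongest reply is that the section opens by naming the pilot as the basis, that the 50% is exactly the pilot's figure, and that reference 5 comes second. The pilot patients were randomised and met the trial's criteria. This stands: the pilot is relevant evidence. It is also very imprecise, and the reference adds nothing to it at 3 weeks.

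The word conservatively can fairly be read as describing the 50%/80% pair, since the planned difference was cut from 33.3 to 30 points. That also stands. It does not make the control rate itself conservative, because that rate was not moved.

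Some stronger readings are tempting but not supported:

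- A reader might infer that the pilot counted a different endpoint, mere tube removal. The section speaks of successful extubation for the controls and gives a decannulation success rate for both arms. Its silence on the time point and the 72-hour rule, in a condensed article, is not a contradiction. The pilot's calendar span, October 2024 to January 2025, is not an outcome window.
- A reader might project the 59% at 12 months back to 3 weeks and conclude that the true control rate is far below 50%. That needs an assumed hazard. It also compares all stroke patients with a tracheotomy with a selected group (aged 70 or under, stable, Glasgow Coma Scale at least 12, following commands) whose 3 weeks are those of the trial intervention.
- A reader might infer that the power claim depends on the control rate being near 50%. It fails at 50% as well, because of the arithmetic, and a lower control rate need not make it worse.

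**Conclusion.** The point holds in two parts. First, reference 5, as the article itself reports it, does not support a 3-week control rate of 50%. The only relevant support is 6 of 12, with an interval of 21% to 79% and an unstated time point and success rule. Second, the stated 80% power is not delivered even if 50% versus 80% is exactly right: it is about 69% with 30 evaluable patients per arm and about 65% after the planned attrition. The required number before attrition is about 36 to 39 per group, not 26.

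The second part rests only on the article's own inputs and the chi-square test it names. The documents do not show that the true control rate is lower than 50%, nor in which direction that would move power. The figures of 47% and 29% hold only under an assumed constant ratio of 1.6.

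**What to change.** In Sample size calculation:

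1. Remove reference 5 as support for the 3-week control rate, and do not call that rate conservative. If the word is meant for the reduction of the difference from 33.3 to 30 points, say so.
2. Confirm or recount the 24 pilot outcomes under the Primary outcome definition (read at the end of 3 weeks, no reintubation within 72 hours of tube removal), state this, and give both rates with their confidence intervals.
3. Correct the statement that 26 per group are required for 80% power.
4. Keeping 60 patients, state the power for 50% versus 80% as about 69% with all 30 per arm evaluable and about 65% after 15% attrition.
5. Add a sensitivity range over lower control rates with the effect model named: 66% to 69% for a constant 30-point gain; 47% (control 40%) or 29% (control 30%) for a constant ratio of 1.6; higher power if the treated rate stays at 80%.

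The cost is a rewritten paragraph and a check of 24 records already held, with a less favourable power statement. If the sponsor prefers to keep 80% power, the pooled formula gives 39/0.85 = 45.9, so 46 per group and 92 in total, which is 32 more patients.

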### Randomisation and blinding

This study will adopt a stratified block randomized controlled design, with participants randomly assigned to the experimental or control group in a 1:1 ratio. Two stratification factors, age (≤40 years vs. >40 years) and stroke type (ischemic vs. hemorrhagic), will be incorporated into the randomization process to ensure balanced distribution of key prognostic variables between groups. The random allocation sequence will be generated using a computer-based random number generator, and group assignment will be conducted by an individual independent of the study team to ensure allocation concealment.

Owing to the nature of the intervention, blinding of participants and treatment providers will not be feasible. To minimise measurement bias, a strict single-blind design will be employed: all outcome assessments will be conducted by independent, standardised assessors who will remain blinded to group allocation; data entry will be performed by research assistants blinded to group allocation; and statistical analyses will be conducted independently by statisticians not involved in the research team. In addition, all research team members, except those directly administering the intervention, will remain blinded to group allocation throughout the trial.

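### The stated inputs (50% vs 80%, two-sided 0.05, 80% power) need about 39 patients per group, not 26; the 60-patient trial has roughly 63–69% power.

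*Protocol article*

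**What the plan says.** The Sample size calculation section of the protocol article gives all the inputs and the output together. The type I error is "0.05 (two-sided) and statistical power" is set at 80% ("80% were adopted based on literature recommendations"). The planning rates follow: "Assuming an decannulation success rate of 50% in the control group and 80% in the TFRL-IMT group". From these, using PASS 15.0, "the required sample size for each group was calculated to be 26".

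For losses, "an expected attrition rate of 15% was applied" through n/(1 − f), which the section evaluates as 26/(1 − 0.15) ≈ 30 per group. It concludes: "Therefore, the finalised total sample size was determined to be 60".

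Allocation is equal: the Randomisation and blinding section has patients "randomly assigned to the experimental or control group in a 1:1 ratio". The abstract says that the primary outcome "will be compared between groups using the Chi-square test". The Statistical analysis section allows either the chi-square test or Fisher's exact test, two-sided at 0.05.

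**The concern.** A difference of 50% vs 80% at two-sided 0.05 and 80% power is a textbook case that needs close to 40 patients per group. A figure of 26 is too low by more than the choice of formula can explain.

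This calculation is the only justification given for the trial's size on its primary outcome. If 26 is wrong, the 80% power claim is wrong too. A non-significant result could then be read as coming from an adequately powered trial when the chance of missing the assumed effect was well above the declared 20%.

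**Working it through.** **Inputs (all from the protocol article).** Control rate p1 = 0.50, TFRL-IMT rate p2 = 0.80, difference 0.30, two-sided α = 0.05 (z = 1.960), power 80% (z = 0.8416), attrition 15% (Sample size calculation); allocation 1:1 (Randomisation and blinding); chi-square test (abstract), or chi-square or Fisher (Statistical analysis). The mean rate is 0.65. The sum of the two variances is 0.25 + 0.16 = 0.41.

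**Step 1: try to reproduce 26 per group.**

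- Pooled variance (the formula matching the chi-square test): n = [1.960·√(2·0.65·0.35) + 0.8416·√0.41]² / 0.30² = (1.322 + 0.539)² / 0.09 = 38.5, so **39**.
- Unpooled variance: n = (1.960 + 0.8416)²·0.41 / 0.09 = 7.849·0.41 / 0.09 = 35.8, so **36**.
- Arcsine: h = 2(arcsin√0.8 − arcsin√0.5) = 0.6435; n = 2·7.849 / 0.6435² = 37.9, so **38**.
- Continuity-corrected (close to Fisher): n = (38.48/4)·[1 + √(1 + 4/(38.48·0.30))]² = 44.9, so **45**.

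None of these gives 26. The smallest is 10 patients per group higher.

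**Step 2: look for inputs that would give 26.**

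| Variant | n per group |
|---|---|
| 50% vs 80%, one-sided 0.05 (or two-sided 0.10) | 29 unpooled, 30 arcsine, 31 pooled, 37 corrected |
| Pilot rates 50% vs 83.3%, two-sided 0.05 | 28 unpooled, 31 pooled, 36 corrected |
| Pilot rates 50% vs 83.3%, one-sided 0.05 | 22 unpooled, 24 pooled, 30 corrected |
| 50% vs 85%, two-sided 0.05, pooled | 26.9, so 27 |
| 50% vs 86%, two-sided 0.05, pooled | 25.1, so 26 |

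A value of 26 fits a treatment rate of about 85–86%. That is above even the pilot's 10/12 = 83.3%, while the protocol describes its 80% as conservative.

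**Step 3: power that the design has for 50% vs 80%.** By the pooled formula, power = Φ{[0.30·√n − 1.960·√(2·0.65·0.35)] / √0.41}.

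- n = 26: (1.530 − 1.322) / 0.640 = 0.324, so 62.7%.
- n = 30: (1.643 − 1.322) / 0.640 = 0.501, so 69.2%.

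Exact binomial enumeration was run as a check on the approximation:

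| Evaluable per group | Pooled formula | Exact, uncorrected chi-square | Exact, Fisher |
|---|---|---|---|
| 26 | 62.7% | 65.4% | 53.7% |
| 30 | 69.2% | 69.2% | 59.6% |
| 39 | 80.5% | 81.3% | 73.2% |

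**Step 4: effect for which the design has 80% power.** Solving the pooled formula for p2 with p1 = 0.50 gives about 83.4% at 30 per group and about 85.5% at 26 per group.

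**Step 5: attrition.** 26/0.85 = 30.6, which rounds up to 31, not 30. Conversely, 30·0.85 = 25.5, just short of the protocol's own 26. With the pooled figure, 39/0.85 = 45.9, so 46 per group and 92 in total. Across the four two-sided formulas (36 to 45), the range after attrition is 43 to 53 per group.

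**The case against.** Several points can fairly be made for the plan.

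- **The formula is not fixed.** The protocol names PASS 15.0 but not the procedure, and leaves chi-square or Fisher open. So 39 is the pooled chi-square value and not the only defensible one. This stands, and the required size is best given as 36 to 45. It does not help 26, which lies outside that range.
- **The lower power figure assumes that 15% of patients have no primary outcome.** The outcome is assessed at the end of a 3-week intervention and an intention-to-treat analysis is planned, so all 60 may be counted. This also stands, and the relevant power is then about 69%. That is still 11 points below the claim.
- **The approximation is slightly pessimistic at 26 per group.** Exact chi-square power there is 65%, not 63%. True, but it does not affect the conclusion.
- **The shortfall is modest if the pilot effect is real.** At 50% vs 83.3%, 30 analysed per group gives 79.9% exact chi-square power. This limits the practical harm, provided that no patient is lost and no correction is applied. It does not make the statement correct, because the protocol deliberately plans on 80%.
- **The Discussion calls the trial exploratory.** A small exploratory trial can be justified, but the label does not support an explicit 80% power claim, and the same section promises high-quality evidence.
- **The attrition rounding is one patient per group.** Agreed. It is a side note and carries no weight beside the main error.

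**Conclusion.** The concern holds and must be fixed. The stated 26 per group does not follow from the stated inputs under any of the usual formulas, nor under a one-sided reading. The required number is 39 evaluable per group with the pooled chi-square formula (36 to 45 across formulas). For the assumed 50% vs 80%, the trial has about 63–65% power if 15% are lost and about 69% if all 60 are analysed, using the uncorrected chi-square test. With Fisher's test the figures are about 54% and 60%. The chance of missing the assumed effect is therefore about 31–37%, or 40–46% with Fisher, against a declared 20%.

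The conclusion rests only on inputs printed in the protocol: the two rates, the two-sided 5% level, 1:1 allocation and a simple two-group comparison of proportions. The 26-per-group figures also take the protocol's 15% attrition as loss of the primary outcome.

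**What to change.** Correct the Sample size calculation section. Delete the claim that 26 per group gives 80% power for 50% vs 80%, and state what the planned size provides. For example: with 60 patients (30 per group), the two-sided chi-square test at 0.05 has about 69% power for 50% vs 80% if all are analysed and about 63% if 15% are lost; 80% power is available for 50% vs about 83.4% (30 per group) or about 85.5% (26 per group). Name the formula or PASS procedure used. If Fisher's test may be the primary test, give its lower figures as well. Correct the attrition step too, since 26/0.85 rounds up to 31.

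This costs a wording amendment and a less favourable stated power, with no extra patients. If the sponsor prefers to keep 80% power for 50% vs 80%, the size has to rise to 46 per group, 92 in total, under the pooled formula with 15% attrition. That is 32 patients more than planned.
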